## Abstract

**Objective:**

This study aims to evaluate the efficacy of photodynamic therapy as an adjunct to conventional endodontic treatment in patients with apical periodontitis and fistulas. In this study, a fistula is characterized as a pathological conduit originating from the infected region at the root apex of the tooth, traversing the oral mucosa, and extending to the external surface of the gingiva. This pathological condition frequently complicates the management of endodontic infections, thereby necessitating the evaluation of supplementary therapeutic interventions. The standard treatment for endodontic infections involves thorough disinfection of the root canal system to remove microbial contamination from the canal and surrounding tissues. To potentially augment the efficacy of conventional treatment, aPDT is proposed as a supplementary, non-invasive technique. This innovative technique uses a photosensitizer, which is a light-sensitive dye, in combination with a light source to produce reactive oxygen species. Reactive oxygen species can effectively target and eliminate bacteria in the root canal system, potentially enhancing treatment outcomes.

**Methods:**

The study will involve 140 teeth with apical periodontitis and fistulas. The teeth will be randomly assigned to one of two treatment groups. Group I will receive only the conventional endodontic treatment, which includes root canal cleaning, shaping, and obturation. Group II will undergo the same conventional endodontic treatment, but with an additional step of aPDT. The aPDT procedure involves applying a photosensitizer to the root canal and irradiating it with light to produce reactive oxygen species. Each group will consist of 70 teeth to ensure adequate statistical power. The primary outcome is fistula resolution, assessed clinically at 15 and 30 days post-treatment. The secondary outcome is the comparison of apical radiolucency from periapical radiographs to evaluate healing and reduction of periapical pathology.

**Conclusions:**

The study aims to determine if adding aPDT significantly improves the management of apical periodontitis and overall success rates of endodontic treatment. The results will provide insights into the effectiveness of aPDT as an adjunctive treatment and its potential benefits in clinical practice.

## Introduction

Endodontics is a dental specialty concerned with the etiology, prevention, diagnosis, and management of pathological conditions affecting the dental pulp and their consequences in the periapical region. One of the fundamental principles is the prevention of infection and its control when present. When dental pathology is established, involving the periapical tissues and causing inflammation, it is classified as apical periodontitis. At this stage, the inflammatory response triggers the degradation of periapical tissues due to pathogens associated with the pulp infection. A fistula generally arises from an injury, frequently due to an infection. A dental fistula is a narrow tract that forms from the infected region of the tooth, typically at the root apex, to the external surface of the oral mucosa. This tract acts as a conduit for microorganisms and their byproducts. As the tract becomes filled with exudate, a localized edema may occur on the mucosal surface [1].

Antimicrobial photodynamic therapy—aPDT is a non-invasive treatment modality and ca be used as an adjunct to conventional periodontitis treatment. The objective of the therapy is to eliminate microbial cells through the significant production of reactive oxygen species. This technique targets both bacteria and fungi. The therapy operates through the interaction of a specific light wavelength with a photosensitizer (PS) in the presence of oxygen [2, 3].

The mechanism of action can be described by the Jablonski diagram. The photosensitizer (PS) absorbs visible light, promoting it from the ground singlet state to the singlet excited state, which has a brief lifetime. In this state, the PS can lose energy through non-radiative processes such as fluorescence or undergo intersystem crossing to the triplet state, which has a longer lifetime. From the triplet state, the PS may lose energy via phosphorescence or participate in the generation of reactive oxygen species (ROS) through two distinct mechanisms: Type I reaction, which involves electron transfer to produce free radicals, or Type II reaction, where energy is transferred to molecular oxygen to form singlet oxygen. The occurrence of Type I and Type II reactions is influenced by various factors, including the physicochemical properties of the photosensitizer (PS), such as its quantum yield and absorption spectrum, as well as the characteristics of the microenvironment, including the availability of molecular oxygen and the presence of solvents or other reactive species. [4].

Therefore, aPDT is utilized as an adjunctive treatment in endodontics. This non-invasive approach involves the application of a photosensitizer, which, when activated by a specific wavelength of light, generates reactive oxygen species. These reactive species effectively target and eradicate bacterial cells, including those within biofilms, enhancing the overall effectiveness of endodontic therapy [2, 3, 5, 6].

Phenothiazines are planar amphipathic tricyclic molecules featuring a quaternary intrinsic nitrogen atom and exhibit phototoxic activity against bacteria. In dentistry, phenothiazines are frequently employed as photosensitizers, with methylene blue (MB) and toluidine blue (TB) being key examples. These compounds are heterocyclic dyes comprising two benzene rings conjugated to a nitrogen atom and a sulfur atom. They exhibit significant absorption when exposed to visible light in the 600–660 nm range, which enhances their efficacy in generating reactive oxygen species within biological tissues [4, 7, 8].

The use of methylene blue in antimicrobial photodynamic therapy has demonstrated reliable outcomes. The hydrophilic nature of MB, combined with its low molecular weight and positive charge, facilitates its penetration through the cell walls of microorganisms [9].

It is essential to acknowledge that the antimicrobial efficacy of antimicrobial photodynamic therapy is contingent upon the match between the absorption spectrum of the photosensitizer and the emission spectrum of the light source. The effectiveness is influenced by factors such as the wavelength of the light, irradiance, exposure duration, and the absorption characteristics of the PS [10].

The aggregation of the photosensitizer is another factor influencing the efficacy of aPDT. This phenomenon, known as dimerization, can be controlled using surfactants. Sodium dodecyl sulfate (SDS) has been demonstrated to effectively reduce this aggregation [11]. Some researchers have demonstrated that methylene blue exhibits greater antimicrobial efficacy when dissolved in ethanol or urea solutions compared to water-based solutions. The addition of surfactants, such as SDS, has been shown to mitigate MB aggregation. This results in an increased concentration of monomeric MB and a reduction in aggregate formation, due to enhanced electrostatic and hydrophobic interactions among MB molecules [9, 12].

The use of methylene blue in a SDS solution at a 0.25% resulted in more effective microbial reduction during aPDT against *Candida albicans* compared to MB alone. The study found that MB, when in its monomeric form, was a more potent photosensitizer, with Type II photochemical reactions—involving singlet oxygen—being the most effective mechanism for inactivating *C*. *albicans* [11].

Following the disruption of the biofilm during endodontic therapy, residual bacterial populations may persist within the periodontal pockets, necessitating adjunctive antimicrobial treatment. Successful endodontic treatment requires precise canal instrumentation, effective irrigation, and appropriate intracanal medication. This process encompasses both manual and mechanized techniques, the application of irrigants, intracanal medicaments, and root canal sealers, all of which involve considerable time and resources. Antimicrobial photodynamic therapy (aPDT) may serve as an adjunctive treatment modality for periodontal disease, potentially reducing reliance on systemic antimicrobials and decreasing the risk of developing bacterial resistance [9].

Thus, the aim of this protocol is to evaluate the photodynamic effect of methylene blue in 0.25% SDS for the treatment of apical periodontitis in presence of fistula. The hypothesis to be tested is that both interventions will exhibit equivalent efficacy, with no statistically significant difference. The evaluation will focus on the resolution of the fistula and the improvement of radiographic indicators, assessed at 15 and 30 days post-endodontic treatment for apical periodontitis [13].

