## Materials and methods

### Study design

This study will be a two-arm, single-center, double-blind, randomized controlled clinical trial with a 1:1 allocation ratio. Upon approval of the study protocol by the Research Ethics Committee of the Universidad Catolica del Uruguay—UCU, the trial will be conducted involving participants with apical periodontitis and a fistula in single-rooted teeth. Inclusion criteria require initial periapical radiography demonstrating apical radiolucency and fistulography to confirm the presence of the fistula. Recruitment will occur at the University Health Clinic of UCU, where the study will be conducted. Participants will be required to read, understand, and sign the Free and Informed Consent Form, which has been approved by the Research Ethics Committee. (211103b).

All participants will receive treatment from a single experienced clinician, who will oversee data collection and procedural execution. Initial periapical radiographs will be required for all participants. Root canal preparation will be conducted using a rotary endodontic device (DENTSPLY). A diode laser apparatus (DMC, THERAPY EC, Sao Carlos, Brazil) with a wavelength of 660 nm, power output of 100 mW, and an irradiation duration of 3 minutes will be utilized [14].

Participants and outcome evaluators will remain blinded to the assigned interventions throughout the study. Unblinding will be permitted only under exceptional circumstances where knowledge of the actual treatment is critical for the ongoing management of the participants.

All participants will receive conventional treatment as described below. Additionally, the study group will undergo antimicrobial photodynamic therapy (aPDT), while the control group will receive a simulation of the laser application. During this process, both participants and the operator will be required to wear protective eyewear.

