### Sample size calculation

The sample size calculation was conducted with the statistical software G-Power 3.1 (Universität Kiel, Germany) applying the chi-square homogeneity test. Identical sample sizes were determined for both the aPDT group and the sham group. A type I error rate of 5% and a statistical power of 80% were specified [15], resulting in a required sample size of n = 70, accounting for a 10% loss to follow-up. The sample size calculation was based on established literature, and a significance level of 5% will be employed [8, 13, 16].

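### The hypothesis is worded as equivalence shown by non-significance, which conflicts with the improvement aim and the difference tests; no equivalence margin is given

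*Protocol article*

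**What the plan says.** The hypothesis is stated once, in the last paragraph of the Introduction: "The hypothesis to be tested is that both interventions will exhibit equivalent efficacy, with no statistically significant difference". The aim just before it is neutral: "the aim of this protocol is to evaluate the photodynamic effect of methylene blue in 0.25% SDS for the treatment of apical periodontitis".

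The Abstract (Conclusions) gives a direction: "The study aims to determine if adding aPDT significantly improves the management of apical periodontitis and overall success rates of endodontic treatment". The Abstract's Objective likewise presents aPDT as a supplement that may add to the effect of conventional treatment.

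The Sample size calculation section was done by "applying the chi-square homogeneity test". It adds: "A type I error rate of 5% and a statistical power of 80% were specified", "resulting in a required sample size of n = 70, accounting for a 10% loss to follow-up". The Abstract (Methods) fixes the unit: "Each group will consist of 70 teeth to ensure adequate statistical power". Study design describes a "randomized controlled clinical trial with a 1:1 allocation ratio", with a simulated laser application as control.

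The Statistical analysis section names the Pearson chi-square, two-sample t and Mann-Whitney tests. The article gives no equivalence margin and no criterion that compares a confidence interval with one.

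**The concern.** The hypothesis sentence names equivalence and gives the absence of statistical significance as its mark. A chi-square test of homogeneity can reject equal proportions. It cannot establish that they are equal or close, because a non-significant result also arises when the trial is too imprecise to see a real difference.

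The sentence also disagrees with the Abstract, which asks whether the add-on improves outcomes. The article therefore holds two readings of what a non-significant result would mean: improvement not shown, or equivalence confirmed. The second could let a worthwhile benefit of aPDT be reported as no benefit, with the published hypothesis cited in support.

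**Working it through.** **Step 1. The statements side by side.**

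- Hypothesis (Introduction): equivalence, marked by non-significance.
- Aim (Introduction): neutral.
- Aim (Abstract, Conclusions): improvement.
- Sizing test: chi-square homogeneity, whose null is equal proportions.
- Analysis tests: all tests of a difference.
- Margin: none.

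Only the hypothesis sentence points to equivalence.

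**Step 2. The plan's own sample size.** No effect size or resolution rate is given, so 70 per arm cannot be reproduced from stated inputs. Assuming an effect size w = 0.25, the noncentral chi-square calculation (1 df, alpha 5%, power 80%) needs N = 126, and 126 / 0.9 = 140, or 70 per arm. With w = 0.20 the total is 219, and with w = 0.30 it is 98. The stated size is thus consistent with a calculation for detecting a difference, but w is back-solved and not documented.

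**Step 3. Evaluable teeth.** 70 × 0.9 = 63 per arm, 126 in total. All resolution rates below are assumptions.

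**Step 4. Chance of non-significance when a difference exists.** For equal arms the noncentrality is λ = N·d² / [4·p̄(1−p̄)].

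- 70% vs 80%: λ = 126 × 0.01 / (4 × 0.1875) = 1.68; power 0.254; non-significant about 75% of the time.
- 70% vs 85%: λ = 126 × 0.0225 / (4 × 0.174375) = 4.06; power 0.522; non-significant about 48%.
- Over other assumed 10-point differences: about 80% (50% vs 60%) and 65% (80% vs 90%).

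The difference detectable with 80% power is about 24 points from a control rate of 50%, 20 points from 70% and 16 points from 80%.

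**Step 5. Precision.** The 95% half-width is 1.96·√[2p(1−p)/63], with p the common rate.

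- p = 0.5: 0.175
- p = 0.7: 0.160
- p = 0.8: 0.140
- p = 0.9: 0.105

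**Step 6. Power of a formal equivalence test.** This uses two one-sided tests at 5%, a true difference of 0 and a normal approximation. Power = max{0, 2Φ(m/SE − 1.645) − 1}, with SE = √[2p(1−p)/63]. For p = 0.8, SE = 0.0713. At m = 0.10, m/SE = 1.40, below 1.645, so power is 0. At m = 0.20, m/SE = 2.81 and power is 0.755.

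The number per arm for 80% power is 2p(1−p)(1.645 + 1.2816)²/m², divided by 0.9 for loss. For p = 0.8 and m = 0.10 this is 275 evaluable after rounding up, or 306 with loss.

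Each cell gives power with 63 per arm, then the number per arm including loss:

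| Rate in both arms | 10 points | 15 points | 20 points |
|---|---|---|---|
| 50% | 0; 477 | 0.031; 213 | 0.452; 120 |
| 60% | 0; 458 | 0.059; 204 | 0.482; 115 |
| 70% | 0; 400 | 0.152; 178 | 0.579; 100 |
| 80% | 0; 306 | 0.354; 136 | 0.755; 77 |
| 90% | 0.179; 173 | 0.755; 77 | 0.964; 44 |

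**The case against.** The strongest reply is that this is a clumsily phrased null. The null is what a test tests, and equal proportions is exactly the null of the planned chi-square. The sham control, the Abstract's aim, the sizing and the analysis all fit a trial of a difference. This reading is plausible and may be what the authors meant. It does not rescue the sentence: a null concerns population proportions, whereas statistical significance is a property of a sample result, and the sentence makes that result the mark of equivalence.

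Several other objections stand.

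- A reader might infer that the protocol sets a decision rule under which imprecision counts as success. No such rule is written. The Statistical analysis section names tests and says nothing on how a non-significant result is to be interpreted. Misreading is a risk, not a stated procedure.
- A reader might infer that every statement of aim is one of superiority. The aim beside the hypothesis is neutral; the direction comes from the Abstract.
- A reader might infer that equivalence power is effectively nil. That holds at a 10-point margin with rates of 50% to 80%. It does not hold across the table, and the documents supply neither margin nor rate.
- The 75% and 48% figures are ordinary low power for differences smaller than the trial can detect. They would remain after rewording. They show why a non-significant result is weak evidence of equivalence, not that the trial is undersized for its purpose.

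**Conclusion.** The hypothesis is misworded and conflicts with the Abstract's aim and with the planned tests. What is affected is the interpretation of a non-significant primary result, not the test or the data collection.

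Under assumed resolution rates of 70% to 80% and 10% loss, such a result would leave an interval of roughly ±14 to ±16 points, too wide to exclude sizeable differences. Across rates of 50% to 90%, equivalence power with 63 per arm is about 0% to 18% at a 10-point margin, 3% to 75% at 15 points and 45% to 96% at 20 points. Of the combinations examined, only a 20-point margin at a 90% rate reaches 80% power within 70 per arm.

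The documents do not support calling this an undersized equivalence trial, since everything outside the one sentence is consistent with testing a difference. The conflict in wording itself rests on no assumed rate. Should be fixed.

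**What to change.** Replace the hypothesis sentence with an explicit pair. The null is that the proportions with fistula resolution are equal in the two arms; the alternative is that they differ, tested two-sided at 5%. Say that the risk difference will be reported with its 95% confidence interval, and that a non-significant result will not be interpreted as equivalence. This costs wording only: the test, the sample size and the data collection stay as planned. It should be done before outcome data are examined by arm.

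If equivalence was truly intended, rewording is not enough. The protocol would need a justified margin, an analysis that compares a confidence interval with that margin (or two one-sided tests), and a restated basis for the sample size. The Abstract's aim would have to change to match. Under most of the margins and rates examined, that would require more than 70 teeth per arm.

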## Materials and methods

### Study design

This study will be a two-arm, single-center, double-blind, randomized controlled clinical trial with a 1:1 allocation ratio. Upon approval of the study protocol by the Research Ethics Committee of the Universidad Catolica del Uruguay—UCU, the trial will be conducted involving participants with apical periodontitis and a fistula in single-rooted teeth. Inclusion criteria require initial periapical radiography demonstrating apical radiolucency and fistulography to confirm the presence of the fistula. Recruitment will occur at the University Health Clinic of UCU, where the study will be conducted. Participants will be required to read, understand, and sign the Free and Informed Consent Form, which has been approved by the Research Ethics Committee. (211103b).

All participants will receive treatment from a single experienced clinician, who will oversee data collection and procedural execution. Initial periapical radiographs will be required for all participants. Root canal preparation will be conducted using a rotary endodontic device (DENTSPLY). A diode laser apparatus (DMC, THERAPY EC, Sao Carlos, Brazil) with a wavelength of 660 nm, power output of 100 mW, and an irradiation duration of 3 minutes will be utilized [14].

Participants and outcome evaluators will remain blinded to the assigned interventions throughout the study. Unblinding will be permitted only under exceptional circumstances where knowledge of the actual treatment is critical for the ongoing management of the participants.

All participants will receive conventional treatment as described below. Additionally, the study group will undergo antimicrobial photodynamic therapy (aPDT), while the control group will receive a simulation of the laser application. During this process, both participants and the operator will be required to wear protective eyewear.

### Interventions

All participants will be treated by the same experienced endodontist, who will oversee both data collection and procedural management. Each participant will receive conventional treatment.

A baseline periapical radiograph will be required for all participants, as well as follow-up radiographs at 15- and 30-days post-treatment. These radiographs will be obtained by a different operator, who will analyze them. This operator will be blinded to the intervention received by each participant.

Conventional treatment will be performed using the Protaper rotary system (Dentsply Maillefer rotary instruments). The canal irrigation will be with 5% sodium hypochlorite, 17% ethylenediaminetetracetic acid, and 2% chlorhexidine [14]. Subsequently, a methylene blue solution in a surfactant medium will be applied using a size 30 paper point cone (Dentsply), with a pre-irradiation time of 1 minute. The study group will receive a 3-minute irradiation period, while the control group will be administered the photosensitizer along with a simulated laser application. This simulation will be achieved by placing an aluminum foil barrier at the tip of the laser equipment to block the light. During these procedures, both the operator and participants will wear protective eyewear to ensure eye safety and concealment. Calcium hydroxide will be applied to the root canals as a long-term intracanal dressing for endodontic treatment.

A diode laser device (Therapy EC, DMC, São Carlos, Brazil) with a wavelength of 660 nm and a power output of 100 mW will be used, according to the parameters detailed in Table 1. The pre-irradiation and irradiation durations will be identical for both groups.

**Table 1 pone.0315169.t001:** Dosimetric parameters.

PARAMETERS	
Wavelength (nm)	660
Operating mode	Continuos
Power (mW)	100
Irradiance (mW/cm^2^)	250
Target irradiated area (cm^2^)	0.4
Exposure time (s)	180
Radiant exposure (J/cm^2^)	10
Energy (J) per point	18
Number of irradiated points	2
Application technique	Entry duct and fistula
Number of sessions	1

The photosensitizer used will be methylene blue at a concentration of 0.005%, dissolved in 0.25% sodium dodecyl sulfate.

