### Blinding

Participants and outcome evaluators will be blinded to the assigned interventions. Unblinding will be permitted only under exceptional circumstances where knowledge of the actual treatment is crucial for the continued management of the participants.

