## Outcome variables

### Primary outcomes

• Resolution of the Fistula: The primary outcome will be the resolution of the fistula, assessed at 15- and 30-days post-treatment. This will be evaluated based on clinical examination and radiographic evidence.

• Radiographic Improvement: The improvement in radiographic signs of apical periodontitis will be assessed at 15- and 30-days post-treatment, focusing on changes in the periapical radiolucency.

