### Statistical analysis

The distribution of data within each group will be checked. The categorical variables will be analyzed using the Pearson Chi-square test or two sample t-test. The correlation between clinical or radiographic findings and the healing fistula will be analyzed by Pearson Chi-square test or Mann Whitney U test [13].

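### The operator who takes the follow-up films also reads them, and the only stated masking is to arm, so sight of the fistula can influence the radiographic score

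*Protocol article*

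**What the plan says.** Under Interventions, the protocol article requires films at three times: "A baseline periapical radiograph will be required for all participants, as well as follow-up radiographs at 15- and 30-days post-treatment". It gives taking and reading to one person, who is not the treating endodontist: "These radiographs will be obtained by a different operator, who will analyze them". The masking of that person is described in one sentence: "This operator will be blinded to the intervention received by each participant". The Blinding section has the same scope: "Participants and outcome evaluators will be blinded to the assigned interventions". Study design says nothing wider. The control arm receives the photosensitizer and a sham made by "placing an aluminum foil barrier at the tip of the laser equipment to block the light".

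The Objective in the Abstract describes the fistula as "traversing the oral mucosa, and extending to the external surface of the gingiva", so its opening lies on a visible surface. Primary outcomes lists both resolution of the fistula and radiographic improvement at 15 and 30 days, the latter "focusing on changes in the periapical radiolucency". No scale or threshold is given. Statistical analysis then plans a test that links the two: "The correlation between clinical or radiographic findings and the healing fistula will be analyzed by Pearson Chi-square test or Mann Whitney U test".

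**The concern.** Masking to arm stops the reader from favouring a known treatment. It does not stop the reader from being influenced by another outcome that may itself respond to treatment. Someone who places a periapical film beside the affected root can see whether the fistula is open or closed, and then judges whether the radiolucency of that tooth has improved. If a closed fistula prompts a more favourable reading, two results are at risk.

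- **Arm comparison of radiographic improvement.** Part of any arm difference in closure would reappear as a radiographic difference. One effect could then be reported as two findings that support each other.
- **Association between film findings and fistula healing.** The reader's knowledge of one variable contaminates the other directly. This needs no difference between arms.

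**Working it through.** The article gives no closure rates, improvement rates or reading error, so there is no figure of its own to reproduce on this point. The size below rests on assumptions.

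**Inputs**
- From the Abstract (Methods): 70 teeth per arm, 140 in total. From Sample size calculation: 10% loss, which leaves 63 per arm, 126 in total.
- Assumed: no true radiographic effect and no true link between film and fistula; 30% of films scored improved when the fistula is open; closure 60% in control and 85% with aPDT; a closed fistula raises the chance of an improved score by h = 0.10, 0.20 or 0.30.

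**Step 1: spurious arm difference.** The expected proportion scored improved in an arm with closure f is 0.30 + f × h. The arm difference is therefore (0.85 − 0.60) × h = 0.25h. The false rejection rate is for a pooled two-proportion test at two-sided 5%, 70 per arm.

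| h | Control | aPDT | Difference | Expected z | False rejection |
|---|---|---|---|---|---|
| 0.10 | 0.360 | 0.385 | 2.5 points | 0.31 | 6% |
| 0.20 | 0.420 | 0.470 | 5.0 points | 0.60 | 9% |
| 0.30 | 0.480 | 0.555 | 7.5 points | 0.89 | 14% |

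Example for h = 0.20: pooled proportion 0.445; SE = √(2 × 0.445 × 0.555 / 70) = 0.084; z = 0.05 / 0.084 = 0.60.

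**Step 2: equal closure.** If closure is the same in both arms, the difference is 0 × h = 0 and the rejection rate stays at 5% for every h.

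**Step 3: spurious association of film and fistula.** Closed teeth: 70 × 0.60 + 70 × 0.85 = 101.5. Open teeth: 140 − 101.5 = 38.5. The comparison is 0.30 + h among closed against 0.30 among open.

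| h | Pooled proportion | SE | Expected z | Two-sided p at that z |
|---|---|---|---|---|
| 0.10 | 0.3725 | 0.0915 | 1.09 | 0.27 |
| 0.20 | 0.4450 | 0.0941 | 2.13 | 0.03 |
| 0.30 | 0.5175 | 0.0946 | 3.17 | 0.002 |

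With 126 teeth, the h = 0.20 case has z = 2.02 (p = 0.044). These values depend only on the total numbers closed and open. They are identical if closure is 72.5% in both arms (140 × 0.725 = 101.5), so this bias does not need an arm difference.

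**Step 4: a second model.** Suppose the reader upgrades a share h of unimproved films when the fistula is closed, and downgrades a share h of improved films when it is open. The spurious difference is then h times the closure difference. With closure 60% against 82%, about the difference detectable with 63 per arm, h = 0.1, 0.2 and 0.3 give 2.2, 4.4 and 6.6 points, with false rejection of about 6%, 8% and 12%. The order of size is the same.

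**The case against.** The strongest reply is that the article nowhere says films are read at the chair, uncoded, or with fistula findings in view. Coding and reading order may be set out in a fuller protocol, and the sentence on taking and analysing films is compatible with coded, later reading. This stands as a limit: a reader might infer that the radiographs are in fact scored unmasked to fistula status, and the text does not establish that. What it does establish is that one person is chosen for both tasks and that the masking it names covers arm alone. That choice creates the exposure unless something further is stated.

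Four other points limit the concern.

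- **Arm masking and sham.** These are stated, and nothing here shows them to fail. The mechanism transfers or exaggerates a closure difference; it cannot create an arm difference alone.
- **Visit order.** A reader might infer that knowing the visit biases the arm comparison. Both arms have the same visits, so it cannot separate them. At most it inflates apparent change over time in both.
- **Secondary outcome.** It is restricted to teeth with healed fistulas, so fistula status hardly varies there and the mechanism has little to act on.
- **Built-in association.** Primary outcomes has fistula resolution judged on radiographs as well as by clinical examination. Part of the association would exist whoever reads the films, and masking the reader does not remove that part.

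It is also fair that no scale is given, so how far the reading is subjective is unknown, and that the Abstract ranks radiolucency as secondary while Primary outcomes lists radiographic improvement as primary.

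**Conclusion.** The concern holds in moderate form. As written, the person who reads the films can see one primary outcome before judging the other, and the stated masking does not cover this.

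For the arm comparison the effect is modest: 2.5 to 7.5 points and false rejection of about 6% to 14% under the assumed 60% against 85% closure and 10 to 30 point shift, and nothing if closure is equal. The association test is more exposed. At a 20-point shift, a link that does not exist would be expected at about z = 2.1, whether or not the arms differ.

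Every closure, improvement and shift value is an assumption. The documents do not support saying that the films will be read unmasked to the fistula, that masking to arm is broken, or that the trial would find a radiographic effect with no difference in closure.

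**What to change.** In the Interventions section, keep the same operator as reader, but state that study scoring is separate from taking the films. Store the films under a code and score them after the last visit, in shuffled order, without access to participant identity, fistula findings or arm.

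Improvement compares films of the same tooth, so the scoring unit must be fixed too. Either give each film an absolute score and derive the change in the analysis, or read the coded films of one tooth together as a set.

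Reconcile the Primary outcomes section as well. While fistula resolution is judged partly on radiographs, part of its association with film findings is built in by definition.

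The cost is the work of coding and shuffling, and study scores that are available only at the end of follow-up. Films viewed for routine care would be looked at separately. No extra reader, film or participant is needed. The article says recruitment starts only after the protocol is accepted for publication, so on its own timetable the change can precede the first participant.
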